### Assessment of telomere length and telomerase activity

Telomere length will be assessed using a quantitative PCR (qPCR)–based assay, and telomerase activity will be evaluated using the telomeric repeat amplification protocol (TRAP) assay, in accordance with SPIRIT recommendations. Peripheral blood mononuclear cells (PBMCs) will be isolated from collected blood samples and processed under standardized laboratory conditions. DNA and protein will be extracted using validated protocols, and commercially available assay kits from the respective manufacturers will be employed. For the qPCR assay, specific primer sequences and appropriate reference genes will be used, with plate layout, internal controls, calibration procedures, and standard curve generation clearly defined. Reaction conditions and cycling parameters will be standardized across all runs. Quality assurance procedures will include duplicate or triplicate measurements, evaluation of intra- and inter-assay variability, and predefined criteria for repeating assays. Telomerase activity will be quantified using a TRAP-ELISA–based approach, incorporating positive and negative controls, with results analyzed using a defined quantification and normalization strategy. These procedures ensure methodological rigor, transparency, and reproducibility of biomarker assessment within the trial.

### Sample size

The primary outcomes of this clinical trial are telomere length, measured in kilobases using quantitative PCR, and telomerase activity, quantified using an ELISA-based TRAP assay. Both are continuous biological markers that reflect cellular aging processes. Sample size estimation was conducted using the formula for comparing two independent means, appropriate for continuous outcomes. Based on pilot findings reported by Ornish et al. (41), a mean difference of 0.5 kb in telomere length between groups was considered clinically relevant, with a standard deviation (SD) of 0.7 kb. A significance level of *α* = 0.05 and power of 80% (*β* = 0.20) were applied in the calculation. Using these parameters, the required sample size per group was obtained, and after accounting for a 10% dropout rate, the final required sample size was determined to be 37 participants per group, resulting in a total of 74 participants for the study. Although Ornish et al. (41) studied men with prostate cancer—a different population from our healthy older adults—we used this data as it provided the most relevant preliminary estimate of variability and effect size available. We acknowledge that this may limit the precision of our sample size calculation and will interpret our findings accordingly. With a significance level of *α* = 0.05 and power of 80% (*β* = 0.20), the required sample size per group was calculated, and after accounting for a 10% dropout rate, the final sample size was determined to be 37 participants per group, for a total of 74 participants. To further strengthen the validity of these assumptions, a dose-finding and feasibility phase will be conducted prior to the full RCT. Data generated from this phase will be used to validate and refine the expected effect sizes, particularly for telomerase activity and cognitive outcomes, thereby enhancing the robustness of the final trial estimates.

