**Outcomes:**

Primary outcomes include telomerase activity and telomere length (qPCR). Secondary outcomes include neurocognitive function [validated MoCA for the Sri Lankan population], neurophysiological functions—nerve conduction test (NCT) for upper and lower limb nerves and brain electrical activity (EEG)—and assessing health-related quality of life (HRQoL) using a validated questionnaire.

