### Method of data analysis

For both primary and secondary outcome measures, mean values at baseline and study completion, as well as mean differences, will be compared across the two study arms using ANOVA (Analysis of Variance) or the non-parametric Kruskal–Walli’s test, depending on the data’s normality. Within each treatment arm, changes in primary and secondary outcomes before and after the intervention will be analyzed using either paired-sample *t*-tests or the non-parametric Wilcoxon signed-rank test, based on the distribution of the data. For all normally distributed outcomes, 95% confidence intervals will be calculated. Categorical variables will be analyzed between groups using the Chi-square test. Potential confounding factors will be adjusted using ANCOVA, with adjusted mean values and corresponding confidence intervals subsequently calculated and reported. Regarding missing data, instead of the last observation carried forward, multiple imputation techniques will be employed to handle missing outcome data, ensuring a more robust and unbiased estimation. Statistical analysis will be conducted using the SPSS software (version 20.0), and the level of significance will be set at *α* = 0.05. In cases of missing outcome data, the most recent available values of the outcome measures will be used as replacements. Intention-to-treat analysis will be applied for all efficacy and safety outcomes. Additionally, per-protocol analysis will be conducted for efficacy outcomes, including only participants who complete the follow-up.

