### Statistical analysis

The statistical analysis plan has been developed to align with the study objectives and ensure rigorous evaluation of outcomes. Descriptive statistics will be used to summarize baseline characteristics across study arms. Continuous primary and secondary outcomes will be assessed for normality prior to analysis. Between-group comparisons of mean changes from baseline to study completion will be conducted using analysis of variance (ANOVA) for normally distributed data or the Kruskal–Wallis test for non-normal data. Within-group pre–post changes will be analyzed using paired-sample *t*-tests or Wilcoxon signed-rank tests, as appropriate.

To account for baseline imbalances and potential confounding factors such as age, sex, and baseline outcome values, analysis of covariance (ANCOVA) will be applied, with adjusted mean differences reported alongside 95% confidence intervals. Categorical variables will be compared between groups using the Chi-square test or Fisher’s exact test, as appropriate.

Missing outcome data will be handled using multiple imputation methods to minimize bias and improve the robustness of estimates. The primary analysis will follow the intention-to-treat principle for all efficacy and safety outcomes, with a secondary per-protocol analysis conducted for efficacy outcomes among participants who complete the follow-up assessments. All statistical analyses will be performed using SPSS software (version 20.0), with a two-sided significance level set at *α* = 0.05.

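### Two unranked primary outcomes are each tested at 5%, with no rule for success and a sample size that covers telomere length only

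*Protocol article*

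**What the plan says.** The Sample size section of the protocol article names two primary outcomes: "The primary outcomes of this clinical trial are telomere length, measured in kilobases using quantitative PCR, and telomerase activity". The abstract, the Outcome measurements section and the section on outcome assessor blinding also list both as primary. None of them puts one ahead of the other or states what combination of results would make the trial positive.

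The sample size rests on one of the two. According to the same section, "a mean difference of 0.5 kb in telomere length between groups was considered clinically relevant", "with a standard deviation (SD) of 0.7 kb", at an undivided alpha of 0.05 and 80% power. After 10% dropout this becomes 37 per group, 74 in total. Telomerase activity gets neither an effect size nor an SD. A feasibility phase is to refine its expected effect, but 74 is already presented as the final number.

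The analysis treats both outcomes alike. Method of data analysis says: "For both primary and secondary outcome measures, mean values at baseline and study completion, as well as mean differences, will be compared" between the arms. Statistical analysis covers all tests "with a two-sided significance level set at *α* = 0.05". Neither section gives an alpha allocation, a testing order or a success rule.

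**The concern.** With two primary outcomes, the trial's error rate and power depend on how the two results combine into one conclusion. The article leaves that open while fixing the level of each test at 5%. Followed as written, a significant telomerase result beside a null telomere-length result could be reported as a positive primary finding, on an outcome the trial was not sized for and at an overall false-positive risk above 5%. If both outcomes were required instead, the 5% level would be safe, but the stated 80% would not describe the power for the trial's claim.

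**Working it through.** **Inputs.** From Sample size: difference 0.5 kb, SD 0.7 kb (standardised effect 0.5/0.7 = 0.714), alpha 0.05, power 80%, dropout 10%. From Statistical analysis: two-sided tests. From Randomization: 1:1 allocation. Not in the article: the correlation between the two outcomes' test statistics, and any effect size or SD for telomerase activity. The correlation is therefore varied, and an equal standardised effect is assumed where one is needed.

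**1. The plan's own figure.**
- Normal formula: n = 2 × SD² × (z₀.₉₇₅ + z₀.₈₀)² / difference² = 2 × 0.49 × (1.960 + 0.842)² / 0.25 = 30.8, so 31 per arm. With dropout, 31/0.9 = 34.4, so 35.
- t-test version: 31.8, so 32 per arm. With dropout, 32/0.9 = 35.6, so 36.
- One-sided version: 25, then 28 with dropout, which is not close.

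The stated 37 is one or two above the two-sided results. It is a full-alpha calculation for one outcome. Enrolling 37 leaves 37 × 0.9 = 33.3, about 33 evaluable per arm. Power for telomere length is then 81.5% (t-test) or 82.7% (normal).

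**2. Either outcome is enough, each at 0.05.** For independent tests the familywise error is 1 − 0.95² = 9.75%. For correlated tests it is 1 − P(|Z₁| < 1.96 and |Z₂| < 1.96) under a bivariate normal:

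| Correlation | Familywise error |
|---|---|
| 0 | 9.75% |
| 0.3 | 9.5% |
| 0.5 | 9.1% |
| 0.8 | 7.8% |
| 0.9 | 7.0% |

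**3. Alpha split equally, 0.025 each.** With 33 evaluable per arm, power for telomere length falls to 72.7% (t-test) or 74.5% (normal). Restoring 80% takes 38 (normal) or 39 (t-test) evaluable per arm, which is 43 or 44 enrolled.

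**4. Both outcomes required, each at 0.05.** The 5% level holds. For power, assume telomerase activity also has a standardised effect of 0.714. With 33 per arm the expected test statistic is 0.714 × √(33/2) = 2.90, and power per outcome is Φ(2.90 − 1.96) = 0.827 (normal approximation). Joint power is 0.827² = 68% at correlation 0. The bivariate normal gives 71% at 0.3, 72% at 0.5 and 76% at 0.8.

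This depends on the assumed effect. With independent outcomes, joint power reaches 80% if the telomerase standardised effect is about 0.94 (normal) or 1.01 (t-test). The article gives no basis for choosing between these cases.

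**5. Fixed order, telomere length first.** Each test uses the full 0.05 and the familywise error stays at 5%. Power for telomere length stays at the 81.5% of step 1 with the planned numbers.

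**The case against.** The best defence is that the article condenses a longer protocol, and that a testing order or success rule is often left to the statistical analysis plan. A two-sided 0.05 level excludes neither a hierarchy nor a both-must-succeed rule, since each of those tests at 0.05. The planned 74 is also compatible with a valid design, as step 5 shows. This stands, and it limits the point: the sample size need not change, and a clarification is enough. It does not remove the point. The article itself fixes the number of primary outcomes, their equal status, the level of each test and the basis of the sample size, and those statements together permit an either-or claim above 5%. An alpha split introduced later would also conflict with the full alpha used in the sample size.

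The planned feasibility phase might supply a telomerase effect size. The article says it will refine that effect, but no starting value is given and 74 is already called final, so the gap remains.

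Three stronger readings are tempting, and the article does not support them.
- A reader might count four primary tests, because Outcome measurements lists assessments at 45 and 90 days. Both analysis sections describe one comparison, from baseline to study completion, and Table 2 schedules the two telomere markers only at baseline and week 12. An assessment time is not a planned test. The disagreement over day 45 is a separate matter to reconcile.
- A reader might infer that the stated 80% power is wrong. It is right for the outcome it was calculated for.
- A reader might infer that power is certainly below 80% if both outcomes are required. That depends on a telomerase effect the article does not give.

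**Conclusion.** The concern holds in this form. The article names two primary outcomes with no ranking or success rule and tests each at two-sided 5%. Under an either-or reading, the familywise error is 9.1% to 9.75% at correlations 0 to 0.5 and 7.8% at 0.8. Calling this nearly double is fair at low to moderate correlation and too strong at high correlation; the article does not say which applies.

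The 37 per arm and the 80% power are correct for telomere length alone. Power for telomerase activity cannot be calculated from the article. Joint power of about 68% to 76% rests on the equal-effect assumption and 33 evaluable per arm. An equal alpha split would leave about 73% for telomere length.

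**What to change.** In Method of data analysis and Statistical analysis, state a fixed testing order at two-sided 5%. Test telomere length first, at a single named primary time point, because it is the outcome the trial is sized on. Test telomerase activity confirmatorily only if the first test is significant. Report all other outcomes and times with confidence intervals and without a confirmatory claim. In Sample size, state that the 80% power refers to telomere length only.

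This costs a few sentences and no extra participants, and keeps about 82% power for telomere length with 33 evaluable per arm. The price is that telomerase activity cannot support a confirmatory claim if telomere length fails. The change should be made before any unblinded result is seen.

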### Recruitment

Individuals interested in participating in this clinical study will receive a detailed Patient Information Leaflet (PIL), which will be accompanied by a verbal explanation of the study procedures. If participants agree with the information provided in the PIL, they will then complete a screening questionnaire. Written informed consent will be obtained from each participant by the investigators prior to the initial interview. During the initial interview, participants will undergo a comprehensive history taking, physical examination, and various hematological and biochemical investigations (including FBS, FBC, ESR, ALT/AST, serum creatinine, and UFR). Recruitment based on MoCA analysis score [the MoCA score of 24 or above (42–47)]. Participants who meet the inclusion and exclusion criteria will be recruited for the study. All baseline assessment forms [including the MoCA analysis form, *Prakriti* analysis (constitution), Quality of Life questionnaire] will be completed by the investigators. Participants will not be permitted to take any other medications during the trial period. If they need to take any additional medications, they must inform the investigators and discontinue participation in the trial.

### Baseline assessment

The Montreal Cognitive Assessment (MoCA) test, the Nerve Conduction Test (NCT), electroencephalography (EEG), constitutional analysis, and health-related quality of life (HRQoL) will be assessed at baseline. Additionally, hematological and biochemical investigations, including fasting blood sugar (FBS), full blood count (FBC), erythrocyte sedimentation rate (ESR), alanine aminotransferase/aspartate aminotransferase (ALT/AST), serum creatinine, and urine full report (UFR), will be conducted.

### Randomization

The randomization sequence will be generated using an online randomization tool.^1^ Block randomization will be applied with blocks of 12 to create a randomization schedule for 74 participants. Patients will be assigned to treatment groups based on the generated sequence. A one-week supply of the assigned investigational product will be distributed to the patients according to their random allocation. The allocation ratio will be 1:1 for each group. Each randomization number’s corresponding allocation will be placed into individually sealed, opaque envelopes. These envelopes, along with the allocation sequence, will be securely stored by an investigator who is not involved in participant recruitment. Participants who meet the inclusion and exclusion criteria will be enrolled in the study and assigned a randomization number sequentially, based on the date and time of their recruitment. The treatment indicated in the sealed envelope for each number will then be provided to the corresponding participant. A flowchart depicting the study design is presented in Figure 1.

**Figure 1 fig1:**
[figure not shown]
Study design. BMND; *Bacopa monnieri* (L.) Wettst normal decoction, BMFD; *Bacopa monnieri* (L.) Wettst freeze dried decoction, BMPD; *Bacopa monnieri* (L.) Wettst phanta decoction (hot infusion). BMD; *Bacopa monnieri* (L.) Wettst freeze dry powder, BMFDP; *Bacopa monnieri* (L.) Wettst freeze dry powder.

## Intervention

### Standardization of dosage

The dosage of *Bacopa monnieri* for the main trial will be standardized based on a preliminary pilot dosing study. This pilot study will involve administering different doses to a small group of participants to evaluate safety, tolerability, and preliminary efficacy. Data collected from this phase will inform the selection of the optimal dose that balances efficacy with safety. Additionally, the selected dose will be supported by phytochemical analysis, ensuring consistency of active constituents such as bacoside A in the prepared decoction. This approach ensures that the dosage used in the main trial is evidence-based, safe, and reproducible.

### Intervention *Bacopa moneri* herbal supplement (BMFD)—Arm 1

BMFD was prepared following the traditional method for decoction preparation (48). Sixty grams of freeze-dried *Bacopa monnieri* (L.) Wettst was boiled with 1920 mL of water over a mild flame until the volume reduced to 240 mL. The decoction was then filtered through a single-folded cotton cloth and collected in a separate vessel. A 60-gram pack of freeze-dried *Bacopa monnieri* (BMFD) will be used to prepare the decoction required for 1 day. A one-week supply, consisting of seven packs, will be provided to each participant. Patients will be instructed to place the supplied herbal pack into a pot, add 1920 mL of water, and simmer it over low heat until the volume is reduced to 240 mL. The preparation process, carried out under standardized conditions, will be demonstrated to participants assigned to the BMFD arm at the clinical trial center of the Faculty of Indigenous Medicine (FIM) through a video. Participants will be instructed to consume a daily dose of 120 mL, taken twice a day before meals.

### Placebo—Arm 2

To prepare the placebo while minimizing antioxidant content, freeze-dried green tea leaves will undergo a repeated steeping process. First, the leaves will be placed in 1920 mL of boiling water and simmered for 30–60 min, after which the liquid will be discarded. This process will be repeated two to three times with fresh water to further reduce the antioxidant content. Afterward, the treated leaves will be freeze-dried to restore their original form. A 60-gram pack of these processed freeze-dried green tea leaves will be used to prepare the placebo decoction for 1 day. The preparation process, carried out under standardized conditions, will be demonstrated to participants in the placebo group at the clinical trial center of FIM through a video. Participants will be instructed to consume a daily dose of 120 mL, taken twice a day before meals. The placebo will be prepared from repeatedly boiled green tea leaves to minimize the presence of caffeine and other bioactive constituents. Although trace amounts may remain, their concentrations will be expected to be negligible and unlikely to produce meaningful cognitive or physiological effects. This method will provide a practical and ethically acceptable placebo that closely matches the appearance and taste of the active preparation while maintaining minimal biological activity.

### Placebo preparation and phytochemical verification

To ensure the validity of the placebo and confirm its phytochemical inertness, the final placebo batch will undergo analytical verification prior to administration. Total phenolic content and antioxidant activity will be assessed using standardized assays such as DPPH and FRAP. Only batches demonstrating negligible or non-detectable antioxidant activity will be approved for use, thereby minimizing any potential biological effects that could influence study outcomes.

The placebo will be prepared using freeze-dried green tea leaves subjected to repeated steeping and exhaustive extraction, a process designed to remove water-soluble polyphenols, flavonoids, and other bioactive constituents while retaining the inert plant matrix. This procedure ensures that the placebo remains biologically inactive while maintaining physical consistency.

To preserve blinding integrity, the placebo will be matched to the BMFD intervention in terms of color, texture, aroma, and mode of preparation. Both BMFD and placebo will be supplied as identically packaged sachets, prepared using the same reconstitution protocol, and presented to participants in a standardized manner to minimize expectancy bias.

### Placebo preparation and justification

The placebo, prepared from repeatedly boiled freeze-dried green tea leaves, has been chosen because it provides a similar color, appearance, and aroma profile to BMFD. To address concerns about residual bioactive components, the final placebo batch will undergo analytical confirmation to ensure that any remaining antioxidant activity or caffeine content is negligible. This process supports the validity of the placebo as an inert control while maintaining blinding integrity.

### Storage, packaging, and dispensing of investigational herbal supplement and placebo

Both products (BMFD and placebo) will be packaged for a 7-day supply and labeled with relevant details, including the batch number, dosage, time of administration, and mode of administration. These packages will be securely stored at the clinical trial center of the Faculty of Indigenous Medicine (FIM), University of Colombo, Sri Lanka, and will be dispensed to participants based on the predetermined randomization sequence. A 7-day supply of the investigational products will be provided to study participants during their weekly visits, along with appropriate instructions (see Table 1).

**Table 1 tab1:** Investigational products.

Herbal supplement	Dose	Mode of administration	Route	Method of preparation
BMFD	120 mL	Morning and evening before meals	Oral	60 g (BMFD) of freeze-dried leaves of plant materials boiled with 1920 mL of water and reduced to 240 ml
Placebo	120 mL	Morning and evening before meals	Oral	Placebo

### Storage, packaging, and dispensing of investigational supplement

#### Outcome measurements

##### Primary outcomes

The following primary outcome measures is assessed at baseline, 45 and 90 days:

Telomerase activity and telomerase length of blood mononuclear cells of participants measured using qualitative polymerase chain reaction (QPCR).

The following secondary outcomes measures are assessed at baseline, 45 and 90 days:

